**Methods:**

The study will involve 140 teeth with apical periodontitis and fistulas. The teeth will be randomly assigned to one of two treatment groups. Group I will receive only the conventional endodontic treatment, which includes root canal cleaning, shaping, and obturation. Group II will undergo the same conventional endodontic treatment, but with an additional step of aPDT. The aPDT procedure involves applying a photosensitizer to the root canal and irradiating it with light to produce reactive oxygen species. Each group will consist of 70 teeth to ensure adequate statistical power. The primary outcome is fistula resolution, assessed clinically at 15 and 30 days post-treatment. The secondary outcome is the comparison of apical radiolucency from periapical radiographs to evaluate healing and reduction of periapical pathology.

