### Sample size calculation

The sample size calculation was conducted with the statistical software G-Power 3.1 (Universität Kiel, Germany) applying the chi-square homogeneity test. Identical sample sizes were determined for both the aPDT group and the sham group. A type I error rate of 5% and a statistical power of 80% were specified [15], resulting in a required sample size of n = 70, accounting for a 10% loss to follow-up. The sample size calculation was based on established literature, and a significance level of 5% will be employed [8, 13, 16].

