## Outcome variables

### Primary outcomes

• Resolution of the Fistula: The primary outcome will be the resolution of the fistula, assessed at 15- and 30-days post-treatment. This will be evaluated based on clinical examination and radiographic evidence.

• Radiographic Improvement: The improvement in radiographic signs of apical periodontitis will be assessed at 15- and 30-days post-treatment, focusing on changes in the periapical radiolucency.

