### Secondary outcomes

• Comparison of Apical Radiolucency: The secondary outcome will involve comparing the apical radiolucency in periapical radiographs of teeth with healed fistulas. This will be assessed before the intervention and at 15 and 30 days post-treatment, focusing on changes in the radiographic appearance of periapical lesions [13].

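### Change in periapical radiolucency is listed as primary in the outcomes section but secondary in the Abstract, and the single 5% error rate and 80% power cannot both hold for two primary outcomes

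*Protocol article*

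**What the plan says.** The protocol article states the status of the radiographic outcome in three places.

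- **Abstract, Methods.** Fistula resolution at 15 and 30 days is the one primary outcome. Radiolucency is secondary: "The secondary outcome is the comparison of apical radiolucency from periapical radiographs to evaluate healing and reduction of periapical pathology".
- **Outcome variables, Primary outcomes.** The heading is plural and has two bullets. The first is fistula resolution, and its text calls this the primary outcome in the singular. The second is headed Radiographic Improvement: "The improvement in radiographic signs of apical periodontitis will be assessed at 15- and 30-days post-treatment, focusing on changes in the periapical radiolucency".
- **Outcome variables, Secondary outcomes.** Radiolucency appears again, in a restricted set of teeth: "The secondary outcome will involve comparing the apical radiolucency in periapical radiographs of teeth with healed fistulas".

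The last paragraph of the Introduction puts fistula resolution and radiographic indicators side by side as the focus of evaluation, without ranking them.

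The Sample size calculation describes one calculation, "applying the chi-square homogeneity test". It adds: "A type I error rate of 5% and a statistical power of 80% were specified". The result is given as "resulting in a required sample size of n = 70, accounting for a 10% loss to follow-up". It names neither the outcome nor the visit, and gives no effect size beyond a pointer to the literature: "The sample size calculation was based on established literature, and a significance level of 5% will be employed".

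**The concern.** The set of primary outcomes determines what the 5% and the 80% refer to. A reader of the Abstract would judge the trial on fistula resolution alone. A reader of the Primary outcomes list could accept a radiographic difference as a primary result. Two primary outcomes tested at 5% each raise the chance of a false claim if either one is enough. They lower the chance of success below 80% if both are needed. Two visits without a lead visit make the first problem larger. With both versions in the text, the document alone does not settle which result decides the trial.

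**Working it through.** **1. Comparing the sections.** The Abstract and the Primary outcomes list contradict each other directly: the same measurement, without restriction, is secondary in one and primary in the other. The Secondary outcomes entry overlaps with both but is not identical to either, because it covers only teeth whose fistula has healed. That subset is defined after randomisation by the other outcome, so it cannot stand in for a comparison of the randomised groups.

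**2. The plan's own sample size.** No effect size is stated, so 70 per group cannot be reproduced from the document's inputs. Working backwards for one chi-square test with 1 degree of freedom:

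- Evaluable teeth: 70 × 0.9 = 63 per group, 126 in total.
- Power = P(noncentral χ² with 1 df and noncentrality N·w² exceeds 3.84). With N = 126 and w = 0.25, noncentrality is 126 × 0.0625 = 7.875 and power is 80.1%.
- Allowing for loss: 126 / 0.9 = 140, or 70 per group.

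So 70 per group fits one test with w = 0.25. That w is inferred from the answer; no section states it.

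**3. If either outcome suffices, one visit.** Each outcome is tested two-sided at 5%. With independent tests the error is 1 − 0.95² = 9.75%. For correlated test statistics (bivariate normal):

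| Correlation | Chance of at least one false positive |
|---|---|
| 0 | 9.75% |
| 0.5 | 9.1% |
| 0.8 | 7.8% |

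**4. If any of two outcomes at two visits suffices.** With four independent tests the error is 1 − 0.95⁴ = 18.5%. By simulation of four normal test statistics, with correlation 0.8 between visits and 0.5 between outcomes, it is about 14%. With 0.8 for both it is 11% to 12%.

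**5. If both outcomes must succeed, one visit.** The error rate stays within 5%. Assuming 80% power for each outcome, joint power is 0.8 × 0.8 = 64% if independent, 69% at correlation 0.5 and 73% at 0.8.

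**6. What two primary outcomes would need.** This step assumes w = 0.25 for both outcomes, which is not stated.

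- Either outcome, Bonferroni at 2.5% each: power for each test at 126 evaluable falls to 71%. Restoring 80% needs 153 evaluable, and 153 / 0.9 = 170 teeth.
- Both outcomes, independent: each needs √0.8 = 89.4% power, which takes 165 evaluable. 165 / 0.9 = 183.3, so 184 teeth.

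The plan has 140.

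**7. Fistula resolution alone at both visits.** With no lead visit, two tests at 5% still give the figures in step 3, now with the correlation between visits. Moving the radiographic bullet therefore does not by itself restore 5%.

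**The case against.** The strongest reply is that the second bullet is simply misplaced. Its text never calls itself primary; only the plural heading does. The first bullet and the Abstract both speak of one primary outcome. This is plausible, and a reader who infers that the trial definitely has two primary outcomes goes further than the document allows. The contradiction still stands, and the document does not say which version governs.

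A second reply is that a rule for multiple outcomes is commonly left to the analysis plan. That is fair, and the absence of such a rule is not the point here. A later rule would still need an agreed list of primary outcomes, and this document gives two.

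A third concerns size. Fistula resolution is itself to be judged partly on radiographic evidence, so the outcomes may be strongly correlated, as may the two visits on the same tooth. This stands: the lower ends of the error ranges are realistic, and 18.5% is a ceiling. The joint-power figures also assume 80% power for the radiographic outcome, which the document does not establish.

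A reader might also infer that the Secondary outcomes entry repeats the primary one, or that the hierarchy will be chosen after the results are seen. The first is inaccurate because of the healed-fistula restriction. The second is unproven: the protocol states that it is registered, and the registry record, not available here, may fix the hierarchy.

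**Conclusion.** The concern holds as an inconsistency that must be reconciled. Radiolucency change without restriction is primary in one section and secondary in another, and one 5% with one 80% cannot serve two primary outcomes. The consequence depends on the success rule:

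- **Either suffices:** error of about 7.8% to 9.8% at one visit, and about 11% to 18.5% over both visits. These are for correlations from 0.8 down to 0, with each test at 5%.
- **Both required:** joint power of about 64% to 73% over the same correlations, assuming 80% power for each outcome.

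It is tempting to read these as a trial with both an inflated error rate and too little power. The document does not support that, because only one of the two can apply. Nor does it show that the calculation was done for fistula resolution: that is a natural inference from the single chi-square test and the Abstract, but the Sample size calculation names no outcome. If fistula resolution at one visit is confirmed as the sole primary outcome and as the outcome that was sized, this point gives no reason to change 70 per group.

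**What to change.** - **Primary outcomes:** keep fistula resolution as the single primary outcome, as in the Abstract. Name one of the two planned visits as the primary time point, with the other visit secondary.
- **Secondary outcomes:** move Radiographic Improvement here, compared in all randomised teeth. Keep the comparison in teeth with healed fistulas as a supportive analysis.
- **Abstract and end of the Introduction:** use the same hierarchy, including the primary time point.
- **Sample size calculation:** state which outcome and time point the calculation was actually done for, and confirm that the 5% and 80% apply to the single primary outcome. The authors must supply this, since the text does not show it.

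The change is to wording only. The protocol says recruitment starts after acceptance for publication, so it can be made before any data exist. The price is that a radiographic benefit, or a benefit at the other visit, can be reported only as a secondary result. If both outcomes are meant to be primary, the success rule must be stated and the sample size recalculated to match.

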### Secondary outcomes

• Comparison of Apical Radiolucency: The secondary outcome will involve comparing the apical radiolucency in periapical radiographs of teeth with healed fistulas. This will be assessed before the intervention and at 15 and 30 days post-treatment, focusing on changes in the radiographic appearance of periapical lesions [13].

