## Materials and methods

### Study design

This study will be a two-arm, single-center, double-blind, randomized controlled clinical trial with a 1:1 allocation ratio. Upon approval of the study protocol by the Research Ethics Committee of the Universidad Catolica del Uruguay—UCU, the trial will be conducted involving participants with apical periodontitis and a fistula in single-rooted teeth. Inclusion criteria require initial periapical radiography demonstrating apical radiolucency and fistulography to confirm the presence of the fistula. Recruitment will occur at the University Health Clinic of UCU, where the study will be conducted. Participants will be required to read, understand, and sign the Free and Informed Consent Form, which has been approved by the Research Ethics Committee. (211103b).

All participants will receive treatment from a single experienced clinician, who will oversee data collection and procedural execution. Initial periapical radiographs will be required for all participants. Root canal preparation will be conducted using a rotary endodontic device (DENTSPLY). A diode laser apparatus (DMC, THERAPY EC, Sao Carlos, Brazil) with a wavelength of 660 nm, power output of 100 mW, and an irradiation duration of 3 minutes will be utilized [14].

Participants and outcome evaluators will remain blinded to the assigned interventions throughout the study. Unblinding will be permitted only under exceptional circumstances where knowledge of the actual treatment is critical for the ongoing management of the participants.

All participants will receive conventional treatment as described below. Additionally, the study group will undergo antimicrobial photodynamic therapy (aPDT), while the control group will receive a simulation of the laser application. During this process, both participants and the operator will be required to wear protective eyewear.

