### Statistical analysis

The distribution of data within each group will be checked. The categorical variables will be analyzed using the Pearson Chi-square test or two sample t-test. The correlation between clinical or radiographic findings and the healing fistula will be analyzed by Pearson Chi-square test or Mann Whitney U test [13].

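### Secondary outcome: comparing radiolucency only in teeth with healed fistulas selects on the primary outcome, so a between-arm comparison there can be biased, most likely against aPDT

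*Protocol article*

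**What the plan says.** The Secondary outcomes section of the protocol article lists one item: "comparing the apical radiolucency in periapical radiographs of teeth with healed fistulas". On timing it adds: "This will be assessed before the intervention and at 15 and 30 days post-treatment".

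The variable that defines this subset is the first primary outcome: "The primary outcome will be the resolution of the fistula, assessed at 15- and 30-days post-treatment". On how resolution is judged, the same section says: "This will be evaluated based on clinical examination and radiographic evidence".

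Radiolucency also appears in two other places without the healed-only limit:

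- Primary outcomes, second item: "The improvement in radiographic signs of apical periodontitis will be assessed at 15- and 30-days post-treatment", with a focus on change in periapical radiolucency.
- Abstract, Methods: "The secondary outcome is the comparison of apical radiolucency from periapical radiographs to evaluate healing and reduction of periapical pathology".

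Statistical analysis does not say which test serves the secondary outcome, or whether that outcome is compared between arms. It does plan an association analysis: "The correlation between clinical or radiographic findings and the healing fistula will be analyzed by Pearson Chi-square test or Mann Whitney U test".

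Interventions requires periapical radiographs at baseline, 15 days and 30 days for all participants.

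**The concern.** The design is a "randomized controlled clinical trial with a 1:1 allocation ratio". Randomisation makes the arms comparable as whole groups. It does not make those teeth in each arm whose fistula later closed comparable with each other.

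If aPDT closes fistulas that would have stayed open under sham, the healed aPDT group contains those harder teeth, and the healed sham group has no counterpart to them. If harder teeth also show less radiographic improvement, the healed aPDT group looks worse on radiolucency for a reason unrelated to any effect of aPDT on bone. The distortion would arise just when aPDT succeeds on the fistula outcome, and the secondary result could then appear to contradict the primary one.

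There is also an inconsistency. One measure stands as a primary outcome with no subset named, as a secondary outcome in healed teeth, and as a secondary outcome with no subset named. A reader cannot tell which comparison will be reported at which rank.

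**Working it through.** **The plan's own figure.** The plan states no figure for this comparison. The nearest is n = 70, which the Abstract makes 70 per group. Sample size calculation gives no healing rates or effect size, so 70 cannot be reproduced from the document's inputs. It is compatible with an assumed effect size w = 0.25, which needs 126 teeth in total, and 126/0.9 = 140. Nothing below tests that figure; only the 10% loss is used, giving 70 × 0.9 = 63 evaluable teeth per arm.

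**Model (assumed).** A tooth heals when a latent standard normal variable exceeds an arm-specific threshold, so that a proportion p heals. Radiographic improvement has SD 1 within each arm, and correlation ρ with that latent variable. Higher values are better. The true effect of aPDT on radiographic improvement is δ.

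**Formula.** With z = Φ⁻¹(1 − p), mean improvement among healed teeth is raised by ρ·φ(z)/p. The healed-only difference, aPDT minus sham, is therefore δ plus

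bias = ρ × [φ(z_aPDT)/p_aPDT − φ(z_sham)/p_sham].

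**Numbers for 60% sham and 80% aPDT.**

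- Sham: z = −0.253, φ(z) = 0.3863, and 0.3863/0.6 = 0.644.
- aPDT: z = −0.842, φ(z) = 0.2800, and 0.2800/0.8 = 0.350.
- Bias per unit of ρ: 0.350 − 0.644 = −0.294.

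| Assumed healing, sham vs aPDT | Bias per unit ρ | ρ = 0 | ρ = 0.3 | ρ = 0.5 | ρ = 0.7 |
|---|---|---|---|---|---|
| 60% vs 60% | 0 | 0 | 0 | 0 | 0 |
| 60% vs 80% | −0.294 | 0 | −0.09 | −0.15 | −0.21 |
| 50% vs 75% | −0.374 | 0 | −0.11 | −0.19 | −0.26 |
| 70% vs 90% | −0.302 | 0 | −0.09 | −0.15 | −0.21 |

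Entries are in SD units. Simulation with 1,000,000 teeth per arm agrees with the closed form. In the same simulation the difference in all teeth equals δ in every scenario, up to simulation error.

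**What this means at 60% vs 80%.**

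- If aPDT prevents no tooth from healing, 0.20/0.80 = 25% of the healed aPDT teeth healed only because of aPDT.
- Teeth compared: 63 × 0.6 ≈ 38 against 63 × 0.8 ≈ 50, so 88 of 126. The other 38 do not enter this analysis.
- A true benefit of 0.20 SD would appear as 0.11, 0.05 or −0.01 SD at ρ = 0.3, 0.5 and 0.7. At 50% vs 75% and ρ = 0.7 it would appear as −0.06 SD.
- With δ = 0, the chance of a significantly worse aPDT result is about 6%, 11% and 20% at the three correlations, against a nominal 2.5% in that tail. Counting both directions it is about 7%, 11% and 20%, against 5%.

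**Do the two conditions fit the documents?** That aPDT may change healing is what the trial is powered to examine. A link between healing and radiolucency is plausible on the protocol's own terms, because resolution is judged partly on radiographic evidence and the association is itself to be analysed. The documents give no value for ρ.

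**The case against.** The strongest reply is that the protocol already contains the unrestricted comparison at a higher rank. Radiographic improvement at 15 and 30 days is a primary outcome with no healed-only limit. A reader might infer from the secondary outcome alone that non-healed teeth drop out of every radiographic analysis; the Primary outcomes section does not support that. This part stands, and it confines the harm to the secondary result.

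Second, the secondary outcome names no arms. Its time points, before treatment and at two visits after, would fit a before/after description within healed teeth, and the planned association analysis fits that reading too. On that reading no randomised comparison is broken. This stands as a possibility. In a two-arm trial whose question is a difference between arms, a between-arm comparison is still the more natural meaning, and the text does not exclude it.

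Third, a reader might go further and conclude that the comparison is biased outright. The documents do not support that. The bias needs both unequal healing and a non-zero correlation. The Introduction words its hypothesis as equivalent efficacy; if healing were equal in both arms, this mechanism would produce no bias.

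Fourth, the healing rates, the correlations and the continuous normal outcome are all assumptions, and the plan also lists chi-square and Mann-Whitney tests. This stands for the size of the bias, less for its existence: changing the test does not remove selection into the healed subset.

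Fifth, an abstract may drop a qualifier for brevity. Accepted for that difference taken alone. Brevity does not explain why change in radiolucency is primary in one section and secondary in the next.

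**Conclusion.** The point holds in conditional form. The secondary outcome is set in a subset that the primary outcome determines after randomisation. Read as a between-arm comparison, it can be biased whenever aPDT changes the healing rate and healing is correlated with radiolucency. The direction is against aPDT if aPDT raises healing and teeth that heal more readily also improve more on the radiograph.

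Under assumed healing of 60% vs 80% the size is about −0.09 to −0.21 SD for correlations of 0.3 to 0.7. Over the three assumed pairs with unequal rates it runs from −0.09 to −0.26 SD. It is zero with equal healing or zero correlation.

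Severity is moderate. It would be tempting to call this a defect that must be corrected before the trial can be interpreted. The documents do not bear that out: the fistula outcome is untouched, and an unrestricted radiographic outcome is already listed as primary. What remains is a secondary result that could mislead, and one measure whose rank and population differ between sections.

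**What to change.** 1. Make any between-arm comparison of radiolucency in all randomised teeth, by assigned arm, at day 15 and day 30. Adjustment for baseline radiolucency is preferable; its details can sit in the analysis plan.
2. Reconcile the Abstract, Primary outcomes and Secondary outcomes so that radiolucency change has one stated rank and one stated population.
3. If a summary in healed teeth is wanted, keep it, label it descriptive, name the visit at which healing is judged, and attach no between-arm test.

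The cost is a few sentences in the outcome definitions. Radiographs at all three time points are already required for every participant, so no visit, measurement or sample-size change is needed.

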### Statistical analysis

The distribution of data within each group will be checked. The categorical variables will be analyzed using the Pearson Chi-square test or two sample t-test. The correlation between clinical or radiographic findings and the healing fistula will be analyzed by Pearson Chi-square test or Mann Whitney U test [13].

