### Interventions

All participants will be treated by the same experienced endodontist, who will oversee both data collection and procedural management. Each participant will receive conventional treatment.

A baseline periapical radiograph will be required for all participants, as well as follow-up radiographs at 15- and 30-days post-treatment. These radiographs will be obtained by a different operator, who will analyze them. This operator will be blinded to the intervention received by each participant.

Conventional treatment will be performed using the Protaper rotary system (Dentsply Maillefer rotary instruments). The canal irrigation will be with 5% sodium hypochlorite, 17% ethylenediaminetetracetic acid, and 2% chlorhexidine [14]. Subsequently, a methylene blue solution in a surfactant medium will be applied using a size 30 paper point cone (Dentsply), with a pre-irradiation time of 1 minute. The study group will receive a 3-minute irradiation period, while the control group will be administered the photosensitizer along with a simulated laser application. This simulation will be achieved by placing an aluminum foil barrier at the tip of the laser equipment to block the light. During these procedures, both the operator and participants will wear protective eyewear to ensure eye safety and concealment. Calcium hydroxide will be applied to the root canals as a long-term intracanal dressing for endodontic treatment.

A diode laser device (Therapy EC, DMC, São Carlos, Brazil) with a wavelength of 660 nm and a power output of 100 mW will be used, according to the parameters detailed in Table 1. The pre-irradiation and irradiation durations will be identical for both groups.

**Table 1 pone.0315169.t001:** Dosimetric parameters.

PARAMETERS	
Wavelength (nm)	660
Operating mode	Continuos
Power (mW)	100
Irradiance (mW/cm^2^)	250
Target irradiated area (cm^2^)	0.4
Exposure time (s)	180
Radiant exposure (J/cm^2^)	10
Energy (J) per point	18
Number of irradiated points	2
Application technique	Entry duct and fistula
Number of sessions	1

The photosensitizer used will be methylene blue at a concentration of 0.005%, dissolved in 0.25% sodium dodecyl sulfate.

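### The analysis section offers a two-sample t-test for categorical variables with no rule for choosing it over the chi-square: negligible harm for a yes/no fistula outcome, about 8% type I error if the radiographic outcome is graded

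*Protocol article*

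**What the plan says.** The Statistical analysis section of the protocol article has three sentences.

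- The first is a preliminary step: "The distribution of data within each group will be checked". It is not tied to any choice of test.
- The second covers categorical data: "The categorical variables will be analyzed using the Pearson Chi-square test or two sample t-test".
- The third concerns association with healing: "The correlation between clinical or radiographic findings and the healing fistula will be analyzed by Pearson Chi-square test or Mann Whitney U test".

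The Sample size calculation section names one test only, "applying the chi-square homogeneity test", with 5% type I error and 80% power.

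The Primary outcomes section lists two outcomes. For the fistula: "The primary outcome will be the resolution of the fistula, assessed at 15- and 30-days post-treatment". For radiographic improvement at the same two visits it gives no scale, only "focusing on changes in the periapical radiolucency". The abstract names fistula resolution alone as primary. The secondary radiographic outcome is described thus: "This will be assessed before the intervention and at 15 and 30 days post-treatment, focusing on changes in the radiographic appearance of periapical lesions". The Interventions section confirms that the films will exist: "A baseline periapical radiograph will be required for all participants, as well as follow-up radiographs at 15- and 30-days post-treatment".

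**The concern.** The sentence on categorical variables is wrong as it stands. A full analysis plan would have to contradict it, not merely add detail. With three or more unordered categories, a t-test result depends on how the categories happen to be numbered. With ordered grades the test can be computed, but it answers a different question from the chi-square, so the two can disagree on the same data.

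The word joining the two tests comes without a decision rule. The choice therefore stays open after the data are seen, and picking the more favourable result raises the type I error above the 5% on which the trial was planned.

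The comparison of arms is also left to inference. The only sentence that names fistula healing relates it to other findings, not to treatment. The between-arm test has to be read out of the generic sentence on categorical variables, which is the faulty one.

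**Working it through.** **1. The plan's own figure.** The article gives 70 teeth per arm, 5% type I error, 80% power and 10% loss, but no effect size or event rates, so 70 cannot be reproduced from its own inputs. Working backwards for a chi-square with one degree of freedom, N = (1.960 + 0.842)² / w² = 7.849 / w². With an assumed w = 0.25, N = 7.849 / 0.0625 = 125.6, rounded up to 126. Then 126 / 0.9 = 140, or 70 per arm. The figure fits a chi-square design with 70 × 0.9 = 63 evaluable teeth per arm, which is used below.

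**2. Yes/no outcome (fistula resolution, apparently binary).** For a 2×2 table with N teeth, the pooled t statistic on 0/1 data is a function of the chi-square: t² = (N − 2)χ² / (N − χ²). At the 5% boundary, χ² = 3.841 and N = 126, so t² = 124 × 3.841 / 122.159 = 3.899 and |t| = 1.975. The two-sided 5% critical value on 124 degrees of freedom is 1.979. The t-test is thus marginally stricter, and having it as an alternative cannot create an extra rejection. Exact binomial enumeration under the null agrees:

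| Evaluable per arm | True rate | Chi-square | t-test | Smaller p | Disagree |
|---|---|---|---|---|---|
| 63 | 0.5 | 5.79% | 4.77% | 5.79% | 1.03% |
| 63 | 0.6 | 5.57% | 5.42% | 5.57% | 0.15% |
| 63 | 0.7 | 5.04% | 5.04% | 5.04% | 0 |
| 63 | 0.9 | 5.07% | 5.07% | 5.07% | 0 |
| 70 | 0.5 | 5.15% | 5.15% | 5.15% | 0 |

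Across all rates tried (0.3 to 0.95, 63 or 70 per arm), the smaller p-value never rejects more often than the chi-square alone.

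**3. Graded outcome (radiographic improvement, if ordinal).** The number of levels and their frequencies are assumptions. The figures are simulated null rejection rates at a nominal 5%, 63 per arm:

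| Assumed level probabilities | Trials | Chi-square | t-test | Smaller of the two |
|---|---|---|---|---|
| .10, .20, .30, .25, .15 | 6,000 | 4.6% | 4.9% | 8.0% |
| .15, .25, .25, .20, .15 | 15,000 | 4.9% | 4.5% | 8.0% |
| .30, .40, .30 | 6,000 | – | – | 7.8% |

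The simulation error at 8% is √(0.08 × 0.92 / 15,000) = 0.2 percentage points, or 0.35 points with 6,000 trials. Each test is sound alone; the excess comes from the free choice. In the second setting, choosing between chi-square and Mann-Whitney also gives 8.0%, and choosing among all three gives 8.2%.

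The choice affects power too. For an assumed common odds ratio of 2.3 on the first five-level scale, power is about 51% with the chi-square and about 74% with either the t-test or Mann-Whitney, which use the ordering.

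**4. Unordered categories.** A constructed table shows the coding problem: 30/15/18 against 20/27/16. The chi-square gives p = 0.062. The t-test gives p = 0.021, 0.109 or 0.381, depending only on how the three categories are numbered. The article names no outcome of this kind, so this shows why the wording is wrong and does not measure harm to a stated outcome.

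**5. Baseline film.** For a continuous radiographic measure with baseline correlation r, covariance adjustment leaves a residual variance of 1 − r² relative to a follow-up-only analysis: 0.91 at r = 0.3, 0.75 at 0.5 and 0.51 at 0.7. A change score gives 2(1 − r): 1.40, 1.00 and 0.60. Adjustment is at least as precise as either. The article gives no r, so these are a range, not an estimate.

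**The case against.** The strongest reply is that this is a drafting slip. The t-test was probably meant for continuous variables, the sentence was over-condensed, and the sample size section shows that the chi-square is the intended test for the main comparison. On that reading fistula resolution is already covered, and step 2 shows that even a literal reading does it no practical harm. That part stands. It limits the size of the point, but the sentence still needs correcting and radiographic improvement still has no clearly assigned test.

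It is also fair that no grade or scale appears anywhere in the article. The 8% and the power figures therefore depend on a scale supplied for the calculation.

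A reader might go further and infer three things that the article does not support:

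- **That the fistula comparison has an inflated error rate.** For a yes/no outcome it does not.
- **That the baseline film is wasted.** Both radiographic outcomes are defined through change, and the secondary one explicitly includes the pre-intervention film. A change score uses it. What is absent is a named baseline-adjusted comparison of arms, which is a matter of efficiency and which an article may leave to a fuller plan.
- **That chi-square or Mann-Whitney is prescribed for comparing serial radiographs between arms.** The third sentence assigns those tests to the association of findings with fistula healing, not to the treatment comparison.

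**Conclusion.** The point holds in a limited form. The article assigns a t-test to categorical variables, which is wrong as written, and leaves the choice against the chi-square open, although only the chi-square underlies the sample size.

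For fistula resolution, taken as yes/no, the effect is negligible. For radiographic improvement, if it is graded on three to five levels and the smaller p-value is taken, the type I error is about 8% instead of 5%. That figure assumes the scale, 63 evaluable teeth per arm and an analyst who uses the freedom in full; it is not a prediction of what the investigators will do. Baseline adjustment is a worthwhile addition, but its gain rests on an assumed correlation. Correcting the section is advisable, and nothing here calls the design or the sample size into question.

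**What to change.** Rewrite the Statistical analysis section as follows:

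1. Delete the t-test as an option for categorical variables.
2. For fistula resolution, name the between-arm Pearson chi-square, with Fisher's exact test if expected counts are small. Report the risk difference with its 95% confidence interval. This matches the test used for the sample size.
3. For radiographic improvement, state the scale and name one between-arm analysis adjusted for the baseline film: ANCOVA if the lesion is measured, ordinal regression with baseline grade if it is graded.
4. Label the association of clinical or radiographic findings with fistula healing as exploratory.

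The cost is a change of wording and slightly more modelling. The films are already scheduled, so no new data are needed, and the sample size does not change because it already rests on the chi-square. The article says that recruitment starts after the protocol is accepted for publication, so the change can be made before any outcome is seen if recruitment has not begun.
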